**CONFIDENTIAL****4.1 Sample size:**

A total of 48 mother-infant couples will be enrolled into the study and randomized in two groups of 24.

**Group 1:** MVA.HIVA administered at 20 weeks of age (n=24)

**Group 2:** Normal EPI vaccine schedule (control group) (n=24)

This study is a pilot study and the immunogenicity analyses will be mainly descriptive. As such, it is not powered to provide definitive evidence of vaccine-induced effects; rather it is based on smaller numbers of participants and will only indicate trends, feasibility, or size of effect and variability of measurements to inform the design of more definitive studies. The rate of serious adverse events will be used as one measure of the safety of the candidate vaccine. Table 2 shows examples of sample size calculations for safety in terms of the ability to detect SAEs, i.e. the probabilities of observing 0, 1+ (1 or more), 2+ or 3+ SAEs among group of n=24 for a range of possible true event rates. If none of the 24 volunteers receiving the vaccine experiences an SAE definitely related to the vaccine, the 95% two-sided upper confidence bound for the rate of such reactions in the population is 13.8% (Table 3).

**Table 2.** Probabilities of detecting events for n=24

| Event rate (SAE) | Detect. Probability (0 events/24 vol's) | Detect. Probability (1+ events/24 vol's) | Detect. Probability (2+ events/24 vol's) | Detect. Probability (3+ events/24 vol's) |
|------------------|-----------------------------------------|------------------------------------------|------------------------------------------|------------------------------------------|
| 0.010            | 0.88                                    | 0.11                                     | 0.01                                     | <0.01                                    |
| 0.025            | 0.74                                    | 0.26                                     | 0.03                                     | <0.01                                    |
| 0.035            | 0.65                                    | 0.35                                     | 0.06                                     | 0.01                                     |
| 0.050            | 0.54                                    | 0.46                                     | 0.12                                     | 0.02                                     |

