### **Visit 3 – VACCINATION VISIT, MVA.HIVA vaccination day (Infant aged 20 weeks $\pm$ 10 days)**

## CONFIDENTIAL

- Subjects will be brought to the vaccine trial clinic.
- Continued consent to participate in the study will be confirmed.
- Inclusion and exclusion criteria will be checked.
- Results of FBC and biochemistry from previous week will be reviewed by the research physician to ensure the child is eligible for randomisation.
- An interim medical history will be taken.
- Physical examination including vital signs (temperature, respiratory rate, pulse rate), and anthropometry (weight, mid left upper arm circumference (MUAC), length) will be performed by the research field worker / research nurse.
- The screening safety profile will be reviewed by the research physician and those children that fulfill all inclusion criteria and no exclusion criteria will be randomised to one of the two study groups by selecting an envelope containing the block randomized treatment group that they are in:
  - **Group 1** infants will receive MVA.HIVA ( $5 \times 10^7$  pfu in no more than 100 µl) intramuscularly into the deltoid muscle of the left arm with a BCG scar. The injection site will be covered after 10 minutes with a sterile dressing that will be removed at the one-hour observation.
  - **Group 2** (control) will not receive any vaccines.
- The infant and parent will remain at the clinical area for one hour following vaccination and will then be allowed to return home.
- The injection site will be inspected at 10 minutes when a dressing will be applied.
- Vital signs will be checked at 30 minutes (+/- 5 min) and 1 hour (+/-10 min) post injection.
- At 1 hour (+/-10 min) the dressing will be removed and discarded. The largest diameter of any induration or redness and any other local reaction at 1 hour will be documented into the CRF. An assessment for possible systemic adverse events (AE's) will be carried out and documented on the CRF, and any concomitant medication documented.
- A nurse / field worker will visit subjects at home daily for the first two days after MVA.HIVA vaccination to record safety and reactogenicity data on a standard CRF form.

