### Visit 4 – FOLLOW-UP VISIT Week 1 (±2 days) post vaccination (Infant aged 21 weeks ± 10 days)

- Subjects will be brought to the vaccine trial clinic.
- Continued consent to participate in the study will be confirmed.
- An interim medical history will be taken.
- Physical examination including vital signs (temperature, respiratory rate, pulse rate), and anthropometry (weight, mid left upper arm circumference (MUAC), length) will be performed by the research field worker / research nurse.
- The injection site will be inspected by the research physician and local reactogenicity including the largest diameter of any induration or redness will be documented into the CRF.
- Adverse events that may have occurred since the infant was vaccinated and any concomitant medications will be documented in the CRF.

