## **9 ASSESSMENT OF SAFETY**

All adverse events (AE) occurring in participants after administration of vaccine will be documented and reported as described below.

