### **9.1 Definitions**

#### **Adverse Event**

An AE is any untoward medical occurrence, including a dosing error, which may occur during or after vaccination. The AE may or may not have a causal relationship with vaccination as indicated by physical signs, symptoms, and/or clinically significant laboratory abnormalities that occur. The definition includes intercurrent illnesses, injuries, exacerbation of pre-existing conditions, and events occurring as a result of product misuse or overdose.

A change in a laboratory variable is considered an AE if it leads to a change in the subject's functional status or if it is considered by the attending physician to be

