## CONFIDENTIAL

and the known biology of the vaccine. The following are guidelines for assessing the relationship of administration of the study vaccine to the AE:

1. NO RELATIONSHIP:

- No temporal relationship to study product; and
- Alternate aetiology (clinical state, environmental or other interventions); and
- Does not follow known pattern of response to study product

2. POSSIBLE:

- Reasonable temporal relationship to study product; or
- Event not readily produced by clinical state, environmental or other interventions; or
- Similar pattern of response to that seen with other vaccines

3. PROBABLE:

- Reasonable temporal relationship to study product; and
- Event not readily produced by clinical state, environment, or other interventions or
- Known pattern of response seen with other vaccines

4. DEFINITE:

- Reasonable temporal relationship to study product; and
- Event not readily produced by clinical state, environment, or other interventions; and
- Known pattern of response seen with other vaccines

Every AE observed or reported from the day of MVA.HIVA injection through to the end of the trial will be recorded on the appropriate CRF.

All AEs will be followed until resolution of the signs or symptoms or laboratory changes occurs, or until a non-study related causality is assigned.

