### **11.2 Expected analyses and outcomes**

#### **11.2.1 Safety of MVA.HIVA**

Determined by comparing adverse events, reactogenicity, haematological and biochemical data from the MVA.HIVA recipients and controls. See Tables 2 and 3 for the probabilities of detecting events given the current trial design.

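### Early adverse-event collection is anchored to an MVA.HIVA injection that controls never receive, which leaves the between-group comparison open to unequal ascertainment of mild early events

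*Protocol*

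**What the plan says.** Section 4.1 sets the design: "A total of 48 mother-infant couples will be enrolled into the study and randomized in two groups of 24". Group 1 is injected at Visit 3 (20 weeks of age); Group 2 receives nothing that day.

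The safety collection is timed as follows:

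- **Section 9:** "All adverse events (AE) occurring in participants after administration of vaccine will be documented".
- **Section 9.1:** an AE is an untoward occurrence "which may occur during or after vaccination".
- **Section 9.2:** the recording window is "Every AE observed or reported from the day of MVA.HIVA injection through to the end of the trial".
- **Section 6.2, Visit 3:** after injection there are vital-sign checks and a systemic AE assessment at one hour. Staff then "will visit subjects at home daily for the first two days after MVA.HIVA vaccination", recording safety and reactogenicity on a standard CRF.
- **Section 6.2, Visit 4:** the look-back is "Adverse events that may have occurred since the infant was vaccinated". Visit 5 uses the same anchor. Visit 6 asks about the time since the previous visit.

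Section 11.2.1 gives the safety analysis: "Determined by comparing adverse events, reactogenicity, haematological and biochemical data from the MVA.HIVA recipients and controls". Safety is a primary objective (section 3), and the Protocol Summary says that the field is not blinded.

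**The concern.** A randomised comparison of AEs needs one time zero and the same means of detection in both groups. Here the recording start, two of the three clinic look-backs and the closest observation all refer to an event that occurs only in Group 1. Section 9.2 and the home-visit sentence name MVA.HIVA itself, so they cannot simply be carried over to controls.

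Minor illness is likely to occur in infants of this age whether or not they are vaccinated. If a mild episode in the first days is noted at a home visit in Group 1, but depends on a parent's memory a week later in Group 2, a harmless vaccine may appear to cause mild early events. With 24 infants per group, a few such episodes colour the safety description. An analysis plan cannot recover control events that were never recorded, so the point must be settled in the protocol before follow-up starts.

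**Working it through.** **No protocol figure to reproduce.** Section 11.2.1 refers to Tables 2 and 3, but these describe SAE counts within one group of 24 and say nothing about ascertainment between groups. The protocol gives neither a background AE rate nor a capture rate.

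**Step 1: which data are exposed.**

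| Data | Collection in the two groups | Exposed? |
|---|---|---|
| One-hour assessment, home visits on days 1 and 2 | Tied to injection; no Group 2 counterpart stated | Yes |
| AE look-back at Visits 4 and 5 | Both groups attend (Table 6); anchor is vaccination | Yes, through the undefined start |
| AE look-back at Visit 6 | Both groups; since the previous visit | No |
| Haematology, biochemistry | One schedule for all infants (Table 7) | No |
| SAEs such as death or hospitalisation | Likely to surface without a home visit | Less |
| Expected local reactions | Kept out of the AE count (9.1) | No meaningful control counterpart |

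**Step 2: possible size in the first week.** All inputs except the number of visit days are assumptions:

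- true first-week risk r = 30% in both groups, with onset spread evenly over 7 days;
- capture c₁ = 90% on intensively observed days and c₀ = 60% by recall at Visit 4;
- d intensively observed days in Group 1: d = 2 for the home-visit days alone, or d = 3 if the injection day is counted as one of the seven.

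Observed risk in Group 1 = r × [d·c₁ + (7 − d)·c₀] / 7. Observed risk in Group 2 = r × c₀ = 0.30 × 0.60 = 18.0%.

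- d = 2: 0.30 × (2 × 0.90 + 5 × 0.60)/7 = 0.30 × 4.8/7 = 20.6%. Ratio 20.6/18.0 = **1.14**.
- d = 3: 0.30 × (3 × 0.90 + 4 × 0.60)/7 = 0.30 × 5.1/7 = 21.9%. Ratio 21.9/18.0 = **1.21**.

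The spurious differences are 2.6 and 3.9 percentage points, or 24 × 0.026 = 0.6 and 24 × 0.039 = 0.9 infants.

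**Step 3: sensitivity.** With s = c₀/c₁, the ratio is 1 + (d/7)(1/s − 1), and r cancels.

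| s | d = 2 | d = 3 |
|---|---|---|
| 0.75 | 1.10 | 1.14 |
| 0.67 (the case above) | 1.14 | 1.21 |
| 0.50 | 1.29 | 1.43 |

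**Step 4: whole follow-up.** Over 16 weeks (112 days) with the same capture rates and two home-visit days, the ratio is (2 × 0.90 + 110 × 0.60)/(112 × 0.60) = 67.8/67.2 = 1.01. The distortion is thus confined to early events.

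**The case against.** The best defence is that the protocol plainly means controls to be followed. They attend Visits 4 to 6 like everyone else, and the vaccination wording in the visit titles serves as a label for both groups. Sections 9 and 9.1 do not name MVA.HIVA. Section 11.1 (Statistical Methods) and section 11.2.1 expressly compare vaccinees with untreated controls. Section 2.3.2 promises all participants regular follow-up at home, and the home-visit sentence speaks of subjects in general. The trial is a pilot with mainly descriptive analyses.

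Much of this stands, and it rules out some stronger readings:

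- A reader might infer that controls have no AE period and would contribute no events. No passage excludes them, and the planned comparison contradicts that reading. Setting a handful of Group 1 events against zero and testing the difference is therefore unwarranted; the protocol also names no safety test.
- A reader might infer a first-week ratio of 0.90/0.60 = 1.5. That treats Group 1 as visited daily all week, whereas only two home visits are planned.
- A reader might conclude that the comparison is certainly biased. The text leaves it open to bias, which is a weaker statement.

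What the defence does not supply is a start day for controls to match section 9.2. Nor does section 2.3.2 give its home follow-up any timing, CRF or AE purpose, all of which the Visit 3 text gives for the post-injection visits. A descriptive analysis is no protection, because unequal capture distorts reported rates as much as it distorts tests.

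**Conclusion.** The point holds as a weakness of specification. AE recording, the Visit 4 and 5 look-backs and the early safety collection hang on an injection given to one group only, while AEs are to be compared between groups in a trial unblinded in the field. This leaves room for unequal ascertainment of mild early AEs. If capture is lower in controls, the error always runs against the vaccine.

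The documents cannot fix its size. On the assumed 90% and 60% capture with even onset, the spurious first-week ratio is about 1.14 to 1.21, which is less than one extra infant among 24 at an assumed 30% risk. Over the whole follow-up it nearly vanishes. The laboratory comparison is untouched, and SAEs are less exposed. The correction is still worth making, because safety is a primary objective and missed control data cannot be recovered.

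**What to change.** 1. In sections 9, 9.1 and 9.2, and in the Visit 4 and 5 look-backs in 6.2, start AE collection at Visit 3 (randomisation) for both groups.
2. Reconcile the Visit 3 text with section 2.3.2: state whether Group 2 receives the home visits on days 1 and 2, recorded on the same CRF.
3. If it does not, limit the between-group AE comparison in 11.2.1 to information collected the same way in both groups: Visits 4 to 6, SAEs and laboratory data. Report the one-hour and day-1/2 findings for Group 1 descriptively.
4. In that case, also state the remaining limitation. Visit 4 recall covers days 1 and 2, and home visits may have prompted it in Group 1, so the restriction reduces the imbalance without removing it. Equal home visits would address this directly.

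**Cost.** Items 1, 3 and 4 are wording. Equal home visits would need 24 × 2 = 48 extra calls. Under item 3, early events found only at home visits leave the comparison, although they are still reported.

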### Contraindications to Vaccination

See section 5.2

### Visit 4 – FOLLOW-UP VISIT Week 1 (±2 days) post vaccination (Infant aged 21 weeks ± 10 days)

- Subjects will be brought to the vaccine trial clinic.
- Continued consent to participate in the study will be confirmed.
- An interim medical history will be taken.
- Physical examination including vital signs (temperature, respiratory rate, pulse rate), and anthropometry (weight, mid left upper arm circumference (MUAC), length) will be performed by the research field worker / research nurse.
- The injection site will be inspected by the research physician and local reactogenicity including the largest diameter of any induration or redness will be documented into the CRF.
- Adverse events that may have occurred since the infant was vaccinated and any concomitant medications will be documented in the CRF.

**CONFIDENTIAL**

- 5 mL of venous blood will be collected for FBC, biochemistry, MVA.HIVA immunogenicity and EPI vaccine antibody assays.
- Appointment at the clinic will be given for 7 weeks time.

**Visits 5 – FOLLOW-UP VISIT, Week 8 ( $\pm$  1 week) post vaccination (Infant aged 28 weeks  $\pm$  10 days)**

- Subjects will be brought to the vaccine trial clinic.
- Continued consent to participate in the study will be confirmed.
- An interim medical history will be taken.
- Physical examination including vital signs (temperature, respiratory rate, pulse rate), and anthropometry (weight, mid left upper arm circumference (MUAC), length) will be performed by the research field worker / research nurse.
- The injection site will be inspected by the research physician and local reactogenicity including the largest diameter of any induration or redness present will be documented into the CRF.
- Adverse events (local and systemic) that may have occurred since the infant was vaccinated and any concomitant medications will be documented in the CRF.
- 5 mL of blood will be collected for HIV testing, FBC, biochemistry and immunogenicity of MVA.HIVA.
- Any child that has developed a positive HIV antibody test as a result of the vaccine will be recalled and tested for HIV by PCR. Assuming they have a negative PCR test, they will have a repeat HIV antibody test at the 9 month visit. If it is still positive at 9 months the test will be repeated every 6 months until they test negative for HIV antibodies.

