**5.1 Inclusion Criteria**

- Healthy infants, 19 weeks of age, with weight for age z-scores within 2 standard deviations of normal.
- Have received all standard EPI immunizations according to national immunization programme (Table 5).
- Written informed consent by parent.
- Mother HIV-1/2-uninfected.

**Table 5.** Overview of EPI vaccination schedule in The Gambia in the first 12 months of life

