**6.1 Laboratory Tests**

**Haematology** Full blood count (FBC) including platelet count

**Biochemistry** Creatinine, alanine transaminase (ALT), alkaline phosphatase (ALP), bilirubin

**MVA.HIVA immunogenicity** Frequency of IFN- $\gamma$  producing cells using ex-vivo and cultured ELISPOT assays after overnight stimulation with pools of 15-mer peptides overlapping by 11 amino acids spanning the length of antigen HIVA.

**EPI immunogenicity** Measurement of vaccine-induced antibody levels to DTwP, Hib, HepB, PCV-7 and OPV.

**Table 7.** Temporal course of infant blood investigations

| Investigation           | Wk 19 | Wk 21 | Wk 28 | Wk 36 |
|-------------------------|-------|-------|-------|-------|
| Haematology             | X     | X     | X     |       |
| Biochemistry            | X     | X     | X     |       |
| MVA.HIVA Immunogenicity | X     | X     | X     | X     |
| EPI Immunogenicity      | X     | X     |       |       |
| HIV test                |       |       | X     |       |
| HLA typing              |       |       |       | X     |

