**Dissemination and explanation of blood results**

All non-immunology blood results will be given and explained to all parents after screening and at follow-up visits. Immunology results will be explained in general terms, for the group and not for individuals, at the end of the study. Those with abnormal blood results at screening will be offered appropriate investigations and treatment or referral as necessary. Parents will receive an explanation of all screening results before proceeding with MVA.HIVA immunization.

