**Visit 6 – FOLLOW-UP VISIT/END OF STUDY, age of 9 months (Infant aged 36  $\pm$  2 weeks)**

- Subjects will be brought to the vaccine trial clinic.
- Continued consent to participate in the study will be confirmed.
- An interim medical history will be taken.
- Physical examination including vital signs (temperature, respiratory rate, pulse rate), and anthropometry (weight, mid left upper arm circumference (MUAC), length) will be performed by the research field worker / research nurse.
- The injection site will be inspected by the research physician and findings documented in the CRF.
- Adverse events (local and systemic) that may have occurred since the last visit and any concomitant medications will be documented in the CRF.
- 5 mL of blood will be collected for immunogenicity of MVA.HIVA and HLA typing.
- EPI vaccines appropriate for age and study group will be given (measles vaccine, yellow fever, OPV)
- Any child that was HIV antibody positive at 28 weeks of age will be re-tested. If the test remains positive they will be given an appointment for repeat testing every 6 months until they become HIV antibody negative.
- Parents will be told that their babies have graduated from the study. Study sticker will be removed from their health cards and children will continue to be offered free health care at Sukuta Health Centre until 3 years of age.

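### Visit 5 makes HIV PCR conditional on the vaccine having caused the positive antibody test, which cannot be known before PCR and does not match Visit 6

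*Protocol*

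**What the plan says.** **Who is tested.** The Visit 5 entry in Protocol section 6.2 states: "5 mL of blood will be collected for HIV testing, FBC, biochemistry and immunogenicity of MVA.HIVA". It makes no distinction by group. Table 6 has both groups bled at 28 weeks. Table 7 ("Temporal course of infant blood investigations", section 6.1) marks the HIV test at week 28 and is not split by group either.

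**What triggers PCR.** Visit 5 then gives the rule: "Any child that has developed a positive HIV antibody test as a result of the vaccine will be recalled" and tested by PCR. It continues: "Assuming they have a negative PCR test, they will have a repeat HIV antibody test at the 9 month visit". If that repeat is still positive, antibody testing goes on every six months until negative.

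**What triggers the later re-test.** Visit 6 says: "Any child that was HIV antibody positive at 28 weeks of age will be re-tested". No cause is mentioned.

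**Who is vaccinated.** Only Group 1 receives MVA.HIVA. Table 4 lists Group 2 as unvaccinated, and the Visit 3 entry for that group includes the words "control) will not receive any vaccines".

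**Who is enrolled.** Section 5.1 requires: "Mother HIV-1/2-uninfected".

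**The concern.** An antibody test cannot say why it is positive. In this trial there are three candidate explanations: antibody induced by the vaccine, infection, and a false-positive result. PCR is the only next test the protocol names, and its purpose is to tell infection from the rest. The Visit 5 rule requires one of those explanations to be accepted before the test that would support it has been done.

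The stake is the care of an individual infant. If site staff applied the sentence exactly as written, an infant whose positive result might mean infection would have an antibody re-test as the next HIV test the schedule requires, at the 9-month visit. PCR would depend on clinical discretion. No estimate, test or sample-size figure is involved.

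**Working it through.** No figure in the plan needs reproducing. The check sets the two visit rules against each kind of infant who could test positive.

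**Inputs**
- Group sizes: 24 and 24 (section 4.1), so 24 + 24 = 48 infants are due for testing at week 28.
- Vaccine exposure: Group 1 only (Table 4; section 6.2, Visit 3).
- PCR trigger: Visit 5. Antibody re-test trigger: Visit 6.
- Nominal gap between the two visits: 36 − 28 = 8 weeks.

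**The two triggers side by side, each read literally**

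| Infant with a positive week-28 antibody test | Meets the Visit 5 PCR trigger | Meets the Visit 6 re-test trigger |
|---|---|---|
| Group 1, antibody induced by the vaccine | Yes | Yes |
| Group 1, positive because of infection | No | Yes |
| Group 1, false positive unrelated to the vaccine | No | Yes |
| Group 2, positive because of infection | No | Yes |
| Group 2, false positive | No | Yes |

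**What follows**
1. No Group 2 infant can satisfy the Visit 5 condition, so its literal reach is at most 24 of 48 infants.
2. Within Group 1, the condition selects the infants whose result is already explained and omits the infected ones, for whom PCR matters most.
3. Nothing in the protocol comes between the antibody result and the PCR that would allow the vaccine to be identified as the cause. The condition therefore cannot be applied as written, even in Group 1.
4. The two visits define what should be one follow-up population in two ways.

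**Do other sections supply the missing step?**
- Section 9.1 counts a laboratory change as an adverse event if the physician judges it clinically significant. A positive HIV antibody test in an infant of an uninfected mother could plausibly qualify.
- Section 9.2 requires adverse events to be followed until they resolve or are attributed to something outside the study. It does not name PCR.
- Section 9.3, on abnormal laboratory values, permits repeat tests and further tests into the cause, but as an option.
- Section 6.1 says "All non-immunology blood results will be given and explained to all parents after screening and at follow-up visits". That secures disclosure, not PCR.
- Section 6.2 offers PCR to children of women who test HIV positive. Enrolled infants have mothers required to be uninfected, and none of the listed study visits after consent includes a maternal re-test.

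These provisions allow PCR, but none mandates it for a seropositive study infant outside the Visit 5 wording.

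**The case against.** The best defence is that nobody would read the sentence literally. It opens by covering any child. The sentence after it treats a negative PCR as an assumption, so infection is still an open question when the child is recalled. If cause had to be proved first, the PCR would serve no purpose. On this view the causal words only name the expected explanation, and Visit 6, which takes in every week-28 positive, shows what was meant. As an account of intent, this stands: PCR for every positive result was probably what the authors wanted. It does not rescue the wording of an operational safety rule, which staff should be able to follow exactly.

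A reader might also infer that controls fall outside adverse-event collection, because sections 9 and 9.2 describe recording by reference to vaccine administration. The protocol does not support that. Section 11.2.1 compares adverse events between MVA.HIVA recipients and controls, and Visits 5 and 6 record them without splitting by group.

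Nor does it follow that a seropositive control would get nothing but an antibody re-test 8 weeks later. Sections 9.1 to 9.3 give a route to further investigation, and a physician could order PCR under them. What remains of the point is narrower: for that infant PCR is discretionary.

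**Conclusion.** The point holds as a minor safety-wording error of low severity. The Visit 5 trigger rests on a cause that is unknown when the rule must be applied. Read literally, it excludes seropositive controls and truly infected vaccinees, and it differs from the Visit 6 trigger.

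The event should be very rare because of the maternal inclusion criterion. It is not excluded: maternal HIV testing is described with the consent process at the 16-week visit, the infant is tested at 28 weeks, and false-positive results can occur. A reader might want to attach a probability to a positive control. The protocol gives no rate of positive antibody tests in unvaccinated infants, so any such figure would only reflect the rate assumed, and none is offered here.

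The conclusion rests on the literal wording and on the absence of any other clause that requires PCR. It does not depend on how many positives occur, and it does not touch the sample size or the safety and immunogenicity analyses.

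**What to change.** In section 6.2, Visit 5, delete the six-word phrase that attributes the positive antibody test to the vaccine. The rule then covers any infant, in either group, with a positive week-28 HIV antibody test: recall and PCR. This is the same population that Visit 6 already uses, so Visit 6 needs no change.

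The cost is a one-phrase amendment and, rarely, one extra recall visit and PCR. No routinely scheduled blood draw is added.
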